### Anthropometric measurements

The following measures will be quantified at the onset and at the end of every intervention period. Actual body weight, visceral fat, body fat, and body muscle percentage will be measured using a commercial body composition monitor and scale (InBody, USA, NO. 770). Body weights will be quantified to the nearest 0.1 kg. Measurements will be taken when participants are without shoes and wearing only light clothing. Their height will be measured to the nearest 0.1 cm with the participants barefoot using a stadiometer (Seca 222). BMI will be calculated as weight in kilograms divided by height in meters squared. Waist circumference measurement will be taken with minimal inspiration at the smallest waist circumference area, rounding up to the nearest 0.1 cm. Waist-to-hip ratio (WHR) will be calculated via standard equations.

### Statistical analysis

All statistical analyses will be performed with the Statistical Package for the Social Sciences (SPSS) (IBM SPSS Statistics for Windows, version 23.0; IBM Corp.), with significance set at *P* < 0.05. Normality of data will be assessed using the Shapiro–Wilk test. The values of continuous variables will be presented as means ± SEM. Categorical data will be presented as number and percentage in study groups. The general linear model repeated measure procedure will be incorporated to compare the quantitative outcome variables between the intervention periods in crude and multivariable adjusted models taking the rolling method and participants’ age, baseline values as between-person factors, and the change in physical activity level, energy intake, and body weight as covariates. The criterion for statistical significance will be defined as *P* < 0.05. Pearson’s correlation coefficient will be applied to show the correlation between biochemical measures and anthropometric indices.

We will analyze the results with intention to treat (ITT) and without participants with non-compliance (study completers). ITT analysis is based on the initial treatment assignment and not on the treatment eventually received. In the ITT method, participant-loss associated bias as well as misallocation or non-adherence of participants is near completely limited. In the case that researchers observe a significant difference between those allocated to receive an intervention and those who actually received that intervention (and adhere to it), per-protocol analysis, which is an additional analysis adjusted for actual treatment, will be performed. The results of the two mentioned analyses will be compared with each other.

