### Eligibility of criteria

Obese and overweight women aged 25–55 years with a body mass index (BMI) of 25–35 kg/m^2^ will be recruited from the Obesity Clinic in Shahid Sadoughi University of Medical Sciences. Exclusion criteria will include: cardiovascular diseases; hepatic, pancreatic, thyroid, or renal problems; having allergies to *N. sativa*; or a history of having a weight-reduction diet or program in the six months before the study. Furthermore, taking any anti-obesity medications or any herbal and anticoagulant agents including aspirin, vitamin E, vitamin K, and warfarin in the six months before the study as well as being either pregnant, lactating, or having uncontrolled polycystic ovary syndrome will also be considered exclusion criteria.

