### Sample size

On the basis of sample size formula suggested for a balanced, crossover designed trials (Fig. 3), considering the non-inferiority margin of δ = 0.05 (clinically meaningful difference), with an expected true difference of 0.02 between the means, and a population variance of 0.01 and considering the significance level of α = 0.05, the sample size to achieve 80% power is calculated to be 35. The final sample size was increased to 40 to accommodate the expected 10% of dropout rate.

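### The adjusted repeated-measures model treats continuous baseline values as factors, which cannot be fitted; with raw continuous terms instead, its treatment test refers to covariate value zero rather than the average difference

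*Protocol article*

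**What the plan says.** The protocol article, Statistical analysis, names SPSS version 23 and the procedure, in two forms: "The general linear model repeated measure procedure will be incorporated to compare the quantitative outcome variables between the intervention periods in crude and multivariable adjusted". Besides a term for the order of treatments, the adjusted model takes "participants’ age, baseline values as between-person factors, and the change in physical activity level, energy intake, and body weight as covariates". So age and baseline values are called factors, and only the three change scores are called covariates.

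Other sections bear on how these terms can enter:

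- Eligibility: "Obese and overweight women aged 25–55 years".
- Randomization and blinding: allocation is stratified by two age bands, 25–40 and 40–55 years, so a two-level age factor already exists.
- Gene expression assay, Biochemical measurements and Anthropometric measurements: the outcomes, and hence their baseline values, are continuous laboratory and body measurements. No cut-points are given for grouping them.
- Sample size: "considering the significance level of α = 0.05, the sample size to achieve 80% power is calculated to be 35", raised to 40 for an expected 10% dropout.

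The text does not say that any continuous term is centred. It also does not say whether the adjusted treatment P value is the within-subject F test or a contrast at the covariate means.

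**The concern.** The trial asks whether outcomes differ, on average in these women, between the N. sativa and placebo periods. With two conditions, this procedure amounts to regressing each woman's treatment difference on the between-person terms, and the within-subject treatment test is the test of the intercept. An intercept describes the point where every continuous term equals zero. If zero lies far from the data, the adjusted P value answers a different question from the crude one, and usually with much less precision.

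The article plans both models and does not rank them. A significant crude result beside a non-significant adjusted one could then be read as an effect explained by the covariates, when it might come only from where zero falls on a measurement scale. The primary outcomes (gene expression and serum concentration of adiponectin, PPAR-γ and TNF-α) would all go through this model.

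**Working it through.** **1. The plan's own figure.** The inputs in Sample size are, for the margin, "considering the non-inferiority margin of δ = 0.05 (clinically meaningful difference"; for the true difference, "with an expected true difference of 0.02 between the means"; for the variance, "a population variance of 0.01". The formula figure is not shown. The usual crossover non-inferiority form with one-sided α = 0.05 is assumed here, and it reproduces the number:

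n = (z₀.₉₅ + z₀.₈₀)² σ² / [2(δ − |μ₂ − μ₁|)²] = 6.18 × 0.01 / (2 × 0.03²) = 34.35, so 35.

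Dropout: 35 / 0.9 = 38.9, so 39 against the stated 40. Completers at 40 enrolled: 40 × 0.9 = 36.

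That 80% belongs to a non-inferiority calculation, not to the treatment test in the adjusted model. Below, 80% is only a benchmark: an effect of 0.48 SD of the within-woman difference, which gives about 80% power in an unadjusted two-sided 0.05 test with 36 women.

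**2. The model as a regression.** For woman i, let Dᵢ be the N. sativa value minus the placebo value:

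Dᵢ = β₀ + β₁·sequenceᵢ + Σ γₖxᵢₖ + eᵢ

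The within-subject treatment test is the test of β₀ = 0. If the x's are centred at their means, β₀ is the average difference. If they are raw, β₀ is the average difference minus Σ γₖ·mean(xₖ), that is, the difference extrapolated to x = 0. A factor has no zero point; its treatment effect is averaged over the levels.

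**3. Baseline literally as a factor.** With 36 women and distinct baseline values there are 36 levels. The intercept plus 35 level contrasts use all 36 observations of D, so the error degrees of freedom are 36 − 36 = 0, before sequence, age and the change scores are added. A few ties would leave a handful at most.

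**4. Raw continuous entry: standard error.** For one raw covariate the standard error of β₀ is multiplied by about √(1 + (mean/SD)²).

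- Age, assumed uniform on 25–55: mean 40, SD 30/√12 = 8.66, ratio 4.62, multiplier √(1 + 4.62²) = 4.73.
- Baseline with coefficient of variation (CV) 0.3, 0.5 or 1.0: ratio 3.33, 2 or 1, multiplier 3.48, 2.24 or 1.41.
- Three independent change scores, each with mean/SD r: multiplier √(1 + 3r²), which is 1, 1.32 and 2 at r = 0, 0.5 and 1.

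**5. Power.** Simulated crossovers, n = 36, true difference 0.48 SD. Sequence and three change scores are in every model (change scores with mean zero unless stated); baseline is lognormal:

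| How the terms enter | Power of the treatment test |
|---|---|
| Age and baseline raw, CV 0.3–1.0 | about 7–9% |
| Age as strata or omitted, baseline raw, CV 0.3 / 0.5 / 1.0 | about 12% / 20% / 42% |
| Age as strata, no baseline, only change scores raw, mean/SD 0 / 0.5 / 1 | about 75% / 51% / 26% |
| Continuous terms mean-centred | about 78–79% |

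Age alone as a two-level factor, with sequence, gives about 78%. With no effect in any woman, the raw test still rejects about 5% of the time.

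**The case against.** The strongest reply is that the article does not specify the harmful model. It calls age and baseline factors, and factors have no zero point. Age has two ready-made strata. The terms actually called covariates are change scores, for which zero is a meaningful value that may lie close to the mean. Centring, and the choice of which output line to report, are details that a condensed article may leave to an analysis plan. The crude model tests the average difference in any case.

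Much of this stands. Age as strata is sound, and the crude analysis is untouched. A reader might infer that the planned adjusted test is definitely made at age zero and baseline zero, so that power falls from 80% to single figures and every adjusted result is uninformative. The documents do not support that: the text does not say that age is continuous or that anything is uncentred, the 80% is not this test's power, and the covariate means and SDs are assumptions. Nor do they support a claim of inflated false positives, which would need an effect that varies with age or baseline while averaging zero; nothing in the article suggests one.

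What the reply does not rescue is baseline. The article states a role for it, and that role cannot be carried out on ungrouped continuous measurements. Grouping would need cut-points that the article does not give, and the ordinary alternative, continuous entry, raises the zero-point problem unless the term is centred. The change scores are also exposed if they do not average zero. This is therefore a fault in what is stated, not only an omitted detail.

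**Conclusion.** The adjusted model is wrong as written. Followed literally it gives no usable test, because baseline as a factor exhausts the error degrees of freedom in about 36 to 40 women. Run with raw continuous terms, it gives a treatment test that need not address the average N. sativa minus placebo difference.

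The algebra in steps 2 to 4 of the check is general. The power figures are illustrations for an effect with about 80% unadjusted power at n = 36, under assumed age, baseline and change-score distributions. The loss runs from slight (change scores raw but averaging zero) to nearly complete (age and baseline both raw). The position of zero for gene expression cannot be judged, because its analysis scale is not stated. The conclusion is confined to the adjusted model.

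**What to change.** In the Statistical analysis section, replace the wording on factors and covariates with text to this effect: age enters as its two randomisation strata (or as a continuous, mean-centred covariate); baseline enters as a mean-centred continuous covariate, not a factor; every other continuous covariate that is retained is mean-centred; the adjusted treatment effect is the N. sativa minus placebo contrast at the covariate means, reported with its 95% CI and P value.

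The cost is a sentence or two and one recoding step in SPSS, with no new data or participants. Trial status reports only that initial recruitment is complete, so the change should be fixed before the data are analysed. Whether the change scores belong in the model at all is a separate question that this wording leaves open.

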**Methods:**

Obese and overweight women aged 25–55 years with a body mass index (BMI) of 25–35 kg/m^2^ will be recruited from the Obesity Clinic in Shahid Sadoughi University of Medical Sciences and will be assessed for eligibility against inclusion criteria. They will be randomly assigned into two groups to receive either two capsules of *N. sativa* or two capsules of placebo per day for eight weeks (each capsule contains 1000 mg of *N. sativa* or placebo). There will be a four-week wash-out period and then participants will receive the reverse supplements for another eight weeks. Biochemical assessments and gene expressions (using real-time polymerase chain reaction) will be conducted at the beginning and at the end of every intervention period.

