### Matching energy intakes between groups

With regard to the dietary energy intakes of participants, we decided to give every individual an iso-energy dietary program in order to match every participant based on their energy and macronutrient intakes. Hence, an eight-week one-to-one individualized iso-energy dietary program for every intervention period, based on every participant’s current weight, will be performed. After determination of required energy, the registered dietician will develop a plan of servings from each food group that will fulfill the macronutrient distribution. The required participants’ daily energy intake will be distributed as follows: < 30% from fat (mainly mono-unsaturated and poly-unsaturated fatty acids); 55% from carbohydrates; and 1.2–1.5 g protein per kg of body weight. After baseline measurements, each participant will meet the registered dietitian three times during each intervention period (at weeks 0, 4, and 8).

Dietary intake will be quantified using three-day food records, including one weekend day and two weekdays as well as 24-h food recalls. Daily macro- and micro-nutrient intakes will be calculated by analyzing food data using nutritionist IV software (First Databank, San Bruno, CA, USA) modified for Iranian foods.

Shahid Sadoughi University of Medical Sciences will be responsible for any related problems; adverse events will be reported to the medical ethics committee from the initiation of the study. Participants may withdraw from the study for any reason at any time.

General information including age, diseases, medications, and supplements will be recorded through interviews at the beginning of the study. Physical activity level will be calculated through a questionnaire using metabolic equivalents (METs) at the beginning and at the end of every intervention period. Results of the assessments will be shared for every participant separately.

Primary outcomes consist of gene expression and serum concentration levels of adiponectin, PPAR-γ, and TNF-α. Secondary outcome measures consist of blood levels of lipid profiles and anthropometric measurements. The assessments of the outcomes are listed below.

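### The stated repeated-measures model does not tie each period's outcome to its own baseline, and it keeps only women with both periods unless missing data are handled elsewhere

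*Protocol article*

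**What the plan says.** The Statistical analysis section of the protocol article gives a single between-treatment comparison: "The general linear model repeated measure procedure will be incorporated to compare the quantitative outcome variables between the intervention periods". It is to be run "in crude and multivariable adjusted models taking the rolling method and participants’ age, baseline values as between-person factors", with "the change in physical activity level, energy intake, and body weight as covariates". The sentence distinguishes factors from covariates and puts baseline among the factors ("age, baseline values as between-person factors"). The *rolling method* is not defined, and no period effect is named.

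The measurement schedule is per period. The abstract says that biochemical and gene-expression assessments "will be conducted at the beginning and at the end of every intervention period". The section on matching energy intakes schedules physical activity "at the beginning and at the end of every intervention period", and the Anthropometric measurements section does the same for body weight.

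The plan promises an ITT analysis and a second analysis without non-compliant women. Of the first it says: "In the ITT method, participant-loss associated bias as well as misallocation or non-adherence of participants is near completely limited". Under Sample size, 35 women are raised to 40 "to accommodate the expected 10% of dropout rate".

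**The concern.** Three parts of the plan do not fit together: the procedure, the roles given to its terms, and the claim made for ITT.

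- A between-person term holds one number per woman, but the quantities to be adjusted for differ between her two periods.
- A repeated-measures general linear model needs every repeated value, so a woman lost after the first period contributes nothing to it. Analysing women as assigned does not restore a missing second period.
- In a two-period crossover, a period effect that is not modelled goes into the error. If the sequences lose different numbers of women, part of it also goes into the treatment estimate.

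This model carries every primary outcome, namely the gene expression and serum levels of the three markers. A mismatch here affects the main result of the trial.

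**Working it through.** **1. The plan's own figure.** The formula sits in a figure that is not shown. The usual crossover non-inferiority form, with one-sided α = 0.05 (an assumption, since sidedness is not stated), gives n = (1.645 + 0.842)² × 0.01 / [2 × (0.05 − 0.02)²] = 34.35, rounded up to 35. This matches. Allowing for dropout, 35 / 0.9 = 38.9, so 39 against the stated 40, which is consistent. The point below does not touch this number. It uses only 40 × 0.90 = 36 expected completers.

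**2. Model against data.** Per woman, the schedule yields two baselines of each outcome and two changes each in activity and weight. Energy-intake change is likewise tied to the two separate dietary programmes. The model text assigns baseline to the between-person level and does not say which period's value is used, or whether both are.

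**3. Baseline as a factor.** A factor with k levels uses k − 1 degrees of freedom. If 36 women have 36 distinct laboratory values, the factor uses 35, which leaves 36 − 36 = 0 for error. A few ties would leave only a few.

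**4. Women dropped.** 40 − 36 = 4 women (10%) leave the comparison.

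**5. Omitted period term.** With n1 and n2 completers in the two sequences, the size of the bias in a crude paired contrast is the period effect × |n1 − n2| / (n1 + n2):

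- 18/18: 0
- 19/17: 2/36 = 0.06 of the period effect
- 20/16: 4/36 = 0.11 of the period effect (0.05 × 4/36 = 0.0056 for a period effect of 0.05)

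For precision at 20/16, with an assumed SD of the difference of 0.10 and period effect of 0.05, the SE ratio is √(0.01 + 0.0025 × 4 × 20 × 16 / 36²) / 0.10 = 1.117, about 12% wider. At 18/18, an analysis with 80% power falls to 78%, 71% and 50% for assumed period effects of 0.25, 0.5 and 1.0 SD of the difference.

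**6. Dropout bias, by simulation.** All inputs are assumed: true difference 0.05, between-woman SD 0.10, SD of the difference 0.10, 40 women, 4 lost after period 1. Mean estimates:

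| Who leaves | Period effect | Crude pairs | Period-adjusted pairs |
|---|---|---|---|
| 4 lowest, all placebo-first | 0.05 | 0.039 (−22%) | 0.044 (−12%) |
| 4 lowest, all placebo-first | 0 | 0.045 (−11%) | not reported |
| 4 at random | 0.05 | 0.050 | 0.050 |
| 2 lowest in each sequence | 0.05 | 0.050 | 0.050 |
| 4 lowest, either sequence | 0.05 | 0.046 | 0.048 |

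In the first scenario an all-data likelihood model with period gave 0.051, unbiased within simulation error. The first two rows come from runs of 400 to 600 trials. Larger repeats shift them by about 0.001 (0.038 and 0.043 in the first row), so the percentages are good to one or two points. The SD of each estimate is about 0.017.

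**The case against.** The best defence is that the text is loose rather than unworkable, and much of that defence stands.

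- **Covariates.** A reader might infer that the procedure cannot carry period-specific values. It can: both periods' values, or their difference, may be entered as separate columns. The text does not say that this is done.
- **Factors.** The word may mean only person-level terms. Age may be the two-level randomisation stratum (25–40 and 40–55 years). The loss of degrees of freedom therefore applies only to laboratory baselines and only on a literal reading, and it would show at the first run.
- **ITT.** A reader might infer that ITT is simply a completer analysis. That is conditional, because imputation may be set in an analysis plan that is not shown. The Compliance section also keeps women who do not complete on the same schedule. Nor do the two analysis sets coincide: a woman with both periods measured but too many capsules left is in the ITT set and outside the second set.
- **Period.** A reader might infer that period is absent from the crude model. The article is silent. If *rolling method* means sequence, its interaction with treatment carries the period effect wherever it is fitted.
- **Size.** The −22% needs all four losses in one sequence, all with the lowest values, plus a period effect that no document supports. Even then the bias of about 0.011 is below one SE (0.017).

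What survives is the mismatch between the stated terms and the per-period data, and the sentence on loss bias. That sentence credits ITT itself with a protection that neither ITT nor this procedure gives.

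**Conclusion.** The point holds as a specification that should be fixed, not as proof that the analysis is invalid. As written, the model does not align outcomes with their own period's baseline and changes. It also loses about 4 of 40 women at the stated dropout rate unless missing data are handled elsewhere, so the claim about loss bias is unsupported.

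The documents do not determine the numerical harm. If dropout is random, or balanced across sequences, bias is about zero and the cost is mainly precision. In the adverse one-sequence scenario, bias is about −11% to −22% of a 0.05 difference. Omitting period adds 0.11 of the period effect at 20/16 completers and no bias when completers are balanced. These sizes rest on the assumed variances, period effect and dropout pattern given above. The stated sample size is not affected by this point.

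**What to change.** - Replace the procedure with a linear mixed model (MIXED in SPSS). Fixed effects: treatment, period, sequence, age stratum and period-specific baseline as a continuous covariate, together with the woman's mean baseline so that within-woman and between-woman effects separate. Random effect: woman.
- If the adjusted model with activity, energy intake and weight is kept, enter each change at its own period's value.
- Make this the ITT analysis, including every randomised woman with at least one on-treatment value. Report complete pairs as a sensitivity analysis.
- State what *rolling method* means.
- Delete or qualify the sentence on participant-loss bias.

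The cost is revised wording and a different procedure, with no new data. The mixed model is valid under a missing-at-random assumption, which should be stated. It does not protect against dropout that depends on unobserved values.
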